## Abstract

**Background:**

Patients with a history of cardiac disease are prone to develop cardiovascular adverse events such as hypotension, hypertension, and tachycardia during anesthesia induction. Therefore, hemodynamic stability is one of the most important concerns for induction of anesthesia in patients undergoing cardiac surgery. Remimazolam tosilate is a new, ultra-short-acting benzodiazepine agent, with the advantages of rapid onset, rapid offset, and minimal cardiorespiratory depression. We aim to compare the effect of remimazolam tosilate and etomidate on hemodynamics during anesthesia induction in patients undergoing valve replacement surgery.

**Methods/design:**

The trial is a prospective, randomized, double-blinded, controlled, single-center trial to compare the effect of remimazolam tosilate and etomidate on hemodynamics in patients undergoing valve replacement surgery. One hundred seventeen patients undergoing selective valve replacement surgery between January 1, 2022, and December 31, 2023, will be enrolled and randomly allocated into one of three groups: low-dose remimazolam group (Group LR), high-dose remimazolam group (Group HR), or etomidate group (Group E). The primary outcome is hemodynamic fluctuations during anesthesia induction (the difference between mean arterial pressure [MAP] to baseline, ▴MAP; and the difference between maximum or minimum heart rate [HR] and baseline, ▴HR). Secondary outcomes include the incidence of adverse cardiovascular events (hypotension, severe bradycardia, hypertension, tachycardia, and arrhythmia), the cumulative doses of vasoactive drugs used per patient, incidence and degree of injection pain and myoclonus, blood glucose values, and vital signs at different time points.

**Discussion:**

This research will determine the effectiveness and safety of remimazolam tosilate induction on hemodynamics in patients undergoing valve replacement surgery.

**Trial registration:**

www.chictr.org.cn identifier ChiCTR2100052535. Registered on 17th Dec 2021, http://www.chictr.org.cn/).

## Background

Patients undergoing cardiac surgery are at risk of developing hemodynamic instability, including hypotension and arrhythmia, especially during the induction of anesthesia. Etomidate is a non-barbiturate hypnotic agent that exerts a sedative and anesthetic effect through γ-aminobutyric acid subtype A (GABA_A_) receptors in the central nervous system [1]. Previous studies have shown that etomidate has minimal side effects on the cardiovascular and respiratory systems [2, 3]. Due to the low risk of hypotension, etomidate is considered to be a relatively safer agent for the induction of anesthesia in patients undergoing cardiac surgery [4, 5]. However, etomidate may result in adrenal cortex function inhibition [6, 7], nausea and vomitin g[8], injection pain [9, 10], and myoclonic movement [11, 12], which have limited its clinical application to a certain extent. Remimazolam tosilate is a new-type benzodiazepine agent, acting on the GABA_A_ receptor, which has been reported to have the advantages of rapid onset, short maintenance and recovery times, and less cardiorespiratory depression [13–15]. Therefore, we hypothesized that remimazolam tosilate may be a relatively safer agent for anesthesia induction in patients undergoing cardiac surgery. Currently, research on the comparison of remimazolam tosilate and etomidate on hemodynamics during anesthesia induction in patients undergoing cardiac surgery is lacking. The aim of this study is to compare remimazolam tosilate and etomidate on the hemodynamics in patients undergoing valve replacement surgery.

## Methods

### Trial design

The trial is a prospective, randomized, controlled, double-blinded, single-center trial designed to evaluate the effect of remimazolam anesthesia induction on hemodynamics in patients undergoing valve replacement surgery. Patients will be enrolled and randomly allocated into one of the three groups: low-dose remimazolam group (Group LR), high-dose remimazolam group (Group HR), or etomidate group (Group E). The trial scheme is illustrated in Fig. 1.

**Fig. 1 Fig1:**
[figure not shown]
Consort flow diagram of the trial design

### Ethics

This study protocol has been approved by the Chinese Ethics Committee of Registering Clinical Trials (Ref: ChiECRCT20210524) and registered on www.chictr.org.cn (ChiCTR2100052535). This trial will be performed according to the principles of the Declaration of Helsinki (Edinburgh 2000 version). Written informed consent will be obtained from each patient before enrollment.

### Sequence generation

All eligible participants will be randomized to one of the three groups (Group LR, Group HR, or Group E ) using computer-generated random numbers and a 1:1:1 allocation ratio. The randomization assignment will be generated by one independent investigator using a computer-generated random number sequence.

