### Participants

#### Study population

Patients who are scheduled to undergo elective valve replacement surgery aged 18–65 years old will be recruited from the Affiliated Hospital of Guizhou Medical University. The trial will be ongoing from January 2022 to December 2023.

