##### Inclusion criteria

American Society of Anesthesiologists (ASA) Physical Status I–III.Patient aged between 18 and 65 years old.

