### Data collection

Each participant’s characteristics, including age, sex, and body weight, as well as ASA grade, type and duration of surgery, vital signs, cumulative doses of vasoactive drugs, and the incidence of adverse events during induction, will be recorded in a designed data form by an investigator who is blinded to this study.

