## Discussion

Patients with cardiac disease often have different degrees of cardiac functional impairment and almost all anesthetic drugs possess capacity to suppress the myocardium and induce vasodilatation, therefore, these patients are prone to developing hypotension during anesthesia induction [17]. Post-induction hypotension is a threatening complication and is associated with increased morbidity and mortality. Considering the importance and impact of hemodynamic changes on complications and outcomes, anesthesiologists should comprehensively consider the effectiveness and safety when selecting anesthetics agents. An ideal induction agent would be one that is easy to administer, has rapid onset and rapid offset, and few adverse effects. However, such an agent does not exist.

Etomidate is a well-known hypnotic agent routinely used for induction of anesthesia [18]. It was previously considered to be superior compared to other anesthetic agents (such as propofol, midazolam, thiopental) for patients with hemodynamic instability owing to its lower inhibition effect on the cardiovascular system [19–21]. However, etomidate may lead to adrenal cortical function inhibition, nausea and vomiting, injection pain, and myoclonic movement, which are some undesirable adverse complications [22, 23]. Therefore, there is a need for anesthetic agents that have a rapid onset of action, short recovery time, and stable cardiovascular profile.

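### The planned ▴MAP and ▴HR comparisons name no stratum or covariate for valve lesion; in arms of 39 this costs precision, and a pre-specified lesion term would recover it

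*Protocol article*

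**What the plan says.** Five places in the protocol article bear on this.

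- **Study population.** The source population is "Patients who are scheduled to undergo elective valve replacement surgery aged 18–65 years old". Neither this section nor the inclusion and exclusion lists restricts the valve replaced, or stenosis versus regurgitation.
- **Inclusion and exclusion criteria.** Severity is limited: "American Society of Anesthesiologists (ASA) Physical Status I–III" is required, and patients with severe cardiac insufficiency, unstable haemodynamics or poorly controlled hypertension are excluded.
- **Sequence generation.** Patients are "randomized to one of the three groups (Group LR, Group HR, or Group E ) using computer-generated random numbers and a 1:1:1 allocation ratio". The section adds: "The randomization assignment will be generated by one independent investigator using a computer-generated random number sequence". No stratification factor is named.
- **Statistical analysis.** Numerical outcomes, which include the primary ▴MAP and ▴HR (changes from baseline), are compared by one-way ANOVA, repeated-measures ANOVA or Kruskal-Wallis. No covariate is named.
- **Data collection.** The form includes "type and duration of surgery, vital signs, cumulative doses of vasoactive drugs". It does not say whether the type of surgery identifies the lesion as well as the valve.

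The Discussion also says: "Patients with cardiac disease often have different degrees of cardiac functional impairment". It links this to a tendency to hypotension at induction.

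**The concern.** The authors expect the underlying cardiac condition to affect what the primary outcome measures. Valve lesion is part of that condition and is known before surgery. It is a plausible source of variation in the pressure and heart-rate response, although the article does not say so. As described, the design does not balance it and the analysis does not adjust for it.

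Two things follow if lesion does predict ▴MAP or ▴HR. Its variance sits in the error term, so the comparison is less sharp than the same patients could give. And if the arms happen to differ in lesion mix, the unadjusted contrast carries that difference, leaving a reader of the single result unsure how much of it is drug.

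**Working it through.** **The plan's own figure.** 31 evaluable per arm with 20% dropout: 31 / 0.8 = 38.75, rounded up to 39; 3 × 39 = 117. This agrees with the article. The 31 cannot be rebuilt, because no effect size or SD is printed. At power 0.90, 31 per arm corresponds to a pairwise difference of 0.82 SD (two-sided 0.05), or Cohen's f = 0.375 for a three-group ANOVA.

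**Assumptions (not in the documents).** Lesion as a two-level factor; prevalence p of 20%, 30% or 50%; lesion effect g of 0.5 to 1.0 SD on the outcome; treatment effect 0.8 SD in one arm.

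**Chance imbalance.** The SD of the difference in lesion share between two arms is about √(2p(1−p)/n). With n = 39:
- p = 0.2: √(0.32/39) = 0.09
- p = 0.3: √(0.42/39) = 0.10
- p = 0.5: √(0.50/39) = 0.11

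Simulating the lesion count over three equal arms (multivariate hypergeometric), the chance of a gap of at least 20 points at 39 per arm is:

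| Gap between | p = 0.2 | p = 0.5 |
|---|---|---|
| One given pair of arms | 3% | 9% |
| Etomidate and either remimazolam arm | 6% | 16% |
| Highest and lowest of the three arms | 8% | 20% |

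The middle row is the relevant one, since the trial's question is remimazolam against etomidate.

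**Effect on a contrast.** Shift = g × imbalance: 0.5 × 0.20 = 0.10 SD and 1.0 × 0.20 = 0.20 SD. Against the implied 0.82 SD this is 0.10/0.82 = 12% to 0.20/0.82 = 24%. The standard error of a pairwise contrast is √(2/39) = 0.23 SD, or √(2/31) = 0.25 SD, so the shift is below one standard error.

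**Type I error over all randomisations.** Simulated at 31 per arm, the unadjusted F test rejected in 4.6% to 5.4% of null trials and the lesion-adjusted test in 4.7% to 5.4%. Both are nominal.

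**Type I error given a 20-point imbalance.** Take 31 per arm, p = 0.5 and a two-sided 5% pairwise test. The test statistic is centred at shift/0.254, with SD √(1 − g²p(1−p)).
- g = 0.5: centre 0.39, SD 0.97; rejection rate about 6%
- g = 1.0: centre 0.79, SD 0.87; rejection rate about 9%

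**Power.** Lesion takes g²p(1−p) of the outcome variance: 0.25 × 0.21 = 5% at p = 0.3, g = 0.5; 1 × 0.21 = 21% at p = 0.3, g = 1.0; 1 × 0.25 = 25% at p = 0.5, g = 1.0. Removing it raises the 0.8 SD effect to 0.8/√0.95 = 0.82, 0.8/√0.79 = 0.90 and 0.8/√0.75 = 0.92 residual SD. In simulation at 31 per arm, power went from about 0.89–0.90 unadjusted to 0.91 (g = 0.5) or 0.95–0.96 (g = 1.0).

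**The case against.** The strongest reply is that randomisation already deals with this. Chance imbalance is part of the sampling error that the test allows for, and the simulations bear that out. If the pilot patients had a similar case mix, between-lesion variance is already in the SD behind the 31 per arm. This stands. A reader might infer that lesion imbalance biases the trial, or cannot be told apart from a drug effect; the documents do not support that. What survives is lost precision and a less clear reading of one realised sample.

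Second, the absence of strata is read from silence in a condensed article. That also stands: the section does not say that randomisation is simple, and the full protocol or analysis plan may name strata or covariates. If so, one sentence settles the point. As printed, though, the named tests are unadjusted.

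Third, a reader might infer that every degree of cardiac impairment is pooled, or that the Discussion names lesion type as prognostic. Neither holds. The eligibility limits remove the severe end, and the Discussion speaks of degree of impairment, never of stenosis or regurgitation. The lesion effect here is an assumption.

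Fourth, the 20% chance of a 20-point gap would overstate the risk: it takes the least favourable mix (50/50) and counts gaps between the two remimazolam arms.

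Finally, stratifying now would split a sequence already in use, since the trial is recruiting. The gain from that is debatable, and it is not recommended here.

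**Conclusion.** The point holds as one of efficiency and clarity, not validity. The article admits all valve lesions within its severity limits, names no stratum, and compares the primary outcomes by tests with no covariate.

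Under the stated assumptions the consequence is modest: a 6% to 16% chance of a 20-point imbalance in an etomidate contrast, a shift of 0.10 to 0.20 SD if it occurs, and up to about six points of power forgone (about one point if the lesion effect is 0.5 SD). All of this depends on lesion prevalence and lesion effect, which the article does not give. If lesion has little bearing on ▴MAP and ▴HR, little is lost. Because adjustment is cheap and leaves type I error nominal, a pre-specified lesion term is better than the unadjusted test as stated.

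**What to change.** 1. Record the valve and the dominant lesion (stenotic, regurgitant or mixed) from the pre-operative record for all patients, including those already enrolled. The mixed level gives multiple-valve patients a place.
2. Before unblinding, pre-specify dominant lesion as a covariate in the ▴MAP and ▴HR models, with ANCOVA in place of one-way ANOVA. Fix the coding, and any collapsing of small levels, at the same time.
3. Leave the running allocation sequence unchanged. State whether it is stratified; if it is, put the stratification factor in the model as well.

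The cost is one extra data-form field and one or two model degrees of freedom, out of 93 − 3 = 90 residual degrees of freedom at 31 per arm. No extra patients or procedures are needed.

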### Allocation concealment mechanism

Numbered-Opaque-sealed envelopes will be used to conceal the allocation information. The nurse who is blinded to the trial will open the opaque-sealed envelopes after the participant’s arrival to the operation room. The opaque-sealed envelopes will be stored in a secure place throughout the study. The operator, anesthesiologists, and outcome investigators will be blind to the allocation information.

### Blinding

The patients, attending anesthesiologist, and nurse, as well as the researchers, will not be aware of the randomization and allocation concealment throughout the study. All syringes containing the experimental medications will be covered with masking tape to conceal the anesthetic information. Data will be analyzed and collected by an investigator who is blinded to the patient’s group allocation.

### Participants

#### Study population

Patients who are scheduled to undergo elective valve replacement surgery aged 18–65 years old will be recruited from the Affiliated Hospital of Guizhou Medical University. The trial will be ongoing from January 2022 to December 2023.

##### Inclusion criteria

American Society of Anesthesiologists (ASA) Physical Status I–III.Patient aged between 18 and 65 years old.

##### Exclusion criteria

Patients who are allergic to or possess contraindications to benzodiazepines, etomidate, opioids, or their components;Patients who participated in other clinical trials within 4 weeks of operation;Severe cardiac insufficiency (acute heart failure, myocardial infarction, etc) or hemodynamic instability;Patients with uncontrolled or poorly controlled hypertension;Abnormal liver and kidney function: ALT and/or exceed 1.5 times of the upper limit of medical reference value; creatinine exceeds the upper limit of medical reference value;Patients with myasthenia gravis or psychiatric disorders (schizophrenia, mania, bipolar disorder, cognitive dysfunction, etc.);Patients with a history of alcohol abuse or addicted to opioids or benzodiazepine; andPatients with expected difficult airway (e.g., thyromental distance ≤4 cm or Mallampati scores of 3 or 4).

##### Drop-out criteria

1. Participant’s request to withdraw the study;

2. Occurrence of serious complications or adverse events during the anesthesia;

3. Difficult intubation; and

4. Other reasons that enable the principal researcher to decide to terminate the study.

### Implementation

After all the participants have finished the preoperative evaluation and screening, participants will be informed of their randomized allocation. Eligibility evaluation and enrolment will be conducted by one independent investigator, while randomization will be finished by another investigator.

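### The Implementation section has participants told their allocation, which contradicts the patient blinding the protocol claims; the nurse who opens the envelopes is also wrongly called blinded

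*Protocol article*

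**What the plan says.** Trial design describes a "prospective, randomized, controlled, double-blinded, single-center trial", and the Abstract uses the same double-blind label.

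On patients, the Blinding section states: "The patients, attending anesthesiologist, and nurse, as well as the researchers, will not be aware of the randomization and allocation concealment throughout the study". The Implementation section states that, after preoperative evaluation and screening, "participants will be informed of their randomized allocation".

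On the nurse, Allocation concealment mechanism says that "envelopes will be used to conceal the allocation information", and then: "The nurse who is blinded to the trial will open the opaque-sealed envelopes". This happens once the participant has reached the operating room. The Blinding section also lists the nurse among those kept unaware.

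On the other roles, Allocation concealment mechanism says: "The operator, anesthesiologists, and outcome investigators will be blind to the allocation information". Interventions has the drugs given by an anesthesiologist blinded to group, and Blinding and Data collection each refer to a blinded investigator who handles the data. For the syringes, Blinding says: "All syringes containing the experimental medications will be covered with masking tape".

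**The concern.** Two statements about who knows the arm cannot be carried out as written.

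The first concerns patients. One section has them told their arm and another has them never know it. Site staff who work from the Implementation section would disclose the allocation before induction, when the patient is awake and about to be asked, in effect, whether the injection hurts. Injection pain is a listed secondary outcome, and the Background and Discussion both name it as a known drawback of etomidate. A patient who knows the arm may therefore have an expectation that acts on the score.

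The second concerns the nurse. A person who opens an envelope to read the allocation cannot be blind to it. If this nurse is treated as blinded because the protocol says so, nothing in the article keeps the nurse away from induction care or from recording outcomes.

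**Working it through.** The plan gives no figure on this point, so the check sets the sections side by side.

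1. **Patients.** Blinding: unaware throughout. Implementation: informed after screening. Both are current operating text, and no third section qualifies either one. They contradict each other directly.

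2. **How many patients.** The Implementation sentence has no exception by group or subset. Planned enrolment is 3 × 39 = 117 (Sample size; Abstract), so if the sentence is followed it applies to all 117. This counts the patients affected. It does not measure bias.

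3. **Envelope-opening nurse.** The envelopes hold the allocation, and the nurse opens them, so the nurse learns the arm. The description of that nurse as blinded in Allocation concealment mechanism fails on its own terms. The Blinding list fails too if it means the same nurse.

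4. **Roles the Implementation sentence does not touch.** Operator, anesthesiologists and outcome investigators (Allocation concealment mechanism), the administering anesthesiologist (Interventions) and the data investigator (Blinding; Data collection) are all still stated to be blind. The documented loss is of patient blinding and of the envelope opener's blinding.

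5. **Which outcomes depend on what the patient knows** (Outcomes):
   - Injection pain: grades 1 and 3 include a verbal complaint. Directly exposed.
   - ▴MAP and ▴HR: extremes of monitored values against baseline, mostly read after loss of consciousness. Probably little exposed.
   - Myoclonus grade: an observer's judgement. Vasoactive drug use: a clinician's action under stated triggers. Bias in either would need an unblinded observer or clinician, and the Implementation sentence does not itself create one.

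6. **Syringe volume.** Doses are 0.2 mg/kg (Group LR) and 0.3 mg/kg (Group HR), a ratio of 0.3 / 0.2 = 1.5. If both were drawn from a single concentration, volume per kg would differ by the same factor of 1.5. If they were diluted to equal volume, the factor would be 1.0. The article states no concentration, so the factor is unknown.

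**The case against.** The strongest reply is that the Implementation sentence is a slip. The Abstract, Trial design, Allocation concealment mechanism, Blinding and Interventions all describe a blinded trial, against one sentence that does not. That reading is plausible, perhaps the likeliest. It does not dispose of the point, because the sentence is an instruction that staff could follow. Nor can it be excused as detail that an article leaves to the full protocol: it is a positive statement that conflicts with another.

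On the nurse, blinded to the trial may simply mean not involved in it, and the nurses in the two sections may be different people. An unblinded person who opens envelopes would not by itself undo a double-blind design. That stands: the fault is in calling this person blinded, not in having such a person.

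A reader might infer more than the article supports:

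- **That no double-blind design remains.** Not supported. The statements keeping the anesthesiologist, outcome investigators and data investigator blind are untouched.
- **That the timing also conflicts.** Not established. Envelopes are opened on arrival in the operating room, which is also after screening, so the two sequences are compatible.
- **That nobody is left who could know the arm and prepare the drug.** Not shown. Sequence generation and Implementation assign sequence generation and randomization to investigators, and who draws up syringes is detail an article may leave out.
- **That the anesthesiologist can tell the two remimazolam arms apart by volume, and that rescue drug use or myoclonus grading is therefore biased.** This rests on a single concentration that the article does not state. Equal-volume preparation is not excluded.

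**Conclusion.** Wrong as written on two counts. The Implementation sentence contradicts the patient blinding set out under Blinding and the double-blind label. The envelope-opening nurse is called blinded although the task reveals the arm.

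The consequence is limited. If the sentence is followed, all 117 planned patients lose blinding before induction. The harm falls mainly on injection pain, a secondary outcome, with probably little effect on ▴MAP and ▴HR. The size of any bias cannot be calculated from the article.

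The conclusion assumes that the Implementation sentence means what it says and that the envelopes show the arm to whoever opens them. The syringe-volume issue remains an open question and is not an established error.

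**What to change.** 1. **Implementation.** Replace the disclosure sentence with one saying that participants are told they will be randomized and do not learn their arm until the study ends.

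2. **Allocation concealment mechanism and Blinding.** Describe the envelope-opening nurse as unblinded and remove this nurse from the list of those kept unaware. State that this nurse takes no part in induction care, rescue decisions or outcome recording. If another nurse is meant in the Blinding list, say so.

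3. **Query to the investigators.** Ask them to confirm that the masked syringes do not reveal the arm by volume, given that the dose per kg differs between Groups LR and HR and no concentration is stated. They should also say whether any participant already enrolled was told the arm.

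**Cost.** The change is to wording and leaves doses, outcomes and sample size as they are. Because recruitment is under way (Trial status), it goes through as an amendment authorized by the ethics committee (Protocol amendments). The practical downside is small: one nurse has to be kept out of induction care, rescue decisions and outcome recording.

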### Interventions

All patients will routinely fast for 8h before surgery. After the patient enters the operating room, standard anesthesia monitoring including electrocardiogram (ECG), noninvasive blood pressure (NIBP), peripheral oxygen saturation (SPO_2_), and bispectral index (BIS) will be routinely monitored. A 20-gauge intravenous cannula will be placed for Ringer lactate (10 ml/kg) infusion. Invasive arterial blood pressure (IBP) will be continuously monitored via insertion of a catheter into the left radial artery under local infiltration anesthesia with lidocaine. After preoxygenation, patients in Group E will be induced with etomidate (0.3 mg/kg), Group LR will be induced with remimazolam (0.2 mg/kg), and Group HR will be induced with remimazolam (0.3 mg/kg). Then, sufentanil (0.5 μg/kg) will be injected in all groups. After that, all patients will be injected with rocuronium (0.6 mg/kg) for muscle relaxation when loss of consciousness. Tracheal intubation will be performed two minutes after rocuronium administration.

Systolic blood pressure (SBP), diastolic blood pressure (DBP), mean arterial pressure (MAP), and heart rate (HR) will be measured and recorded at baseline (T0), 1 min after the induction of anesthesia (T1), 3 min after the induction of anesthesia (T2), immediately at tracheal intubation (T3), 1 min after tracheal intubation (T4), and 5 min after tracheal intubation (T5). Laryngoscopy and anesthesia administration will be performed by an anesthesiologist who is blinded to the study groups. The duration of laryngoscopy and intubation are also recorded for each patient.

Hypotension is considered when MAP falls below 60 mmHg or decreases to less than 20% of baseline during induction, and 50 μg norepinephrine will be given intravenously as needed. When HR decreases below 45 beats per min (bpm), it is considered severe bradycardia and 0.25 mg atropine or more will be administrated by intravenous injection. If the MAP rises above 120 mmHg, nitroglycerin will be given, and once HR rises above 120 bpm, esmolol will be given. The incidence of adverse cardiovascular events (hypotension, severe bradycardia, hypertension, tachycardia, and arrhythmia) and the cumulative doses of vasoactive drugs will be recorded.

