#### Secondary outcomes

The secondary outcomes include the following:The incidence of adverse cardiovascular events (hypotension, severe bradycardia, hypertension, tachycardia, and arrhythmia).The cumulative doses of vasoactive drugs used per patient.Hemodynamic parameters (HR, MAP, SBP, DBP), BIS index, lactic acid, and glucose valuesIncidence and degree of injection pain is measured using a 4-point graded scale: 0 = no pain, 1 = verbal complaint of pain, 2 = withdrawal of the arm, 3 = both verbal complaint and withdrawal of the arm.Incidence and degree of myoclonus is recorded as follows: 0 = no myoclonic movements, 1 = minor myoclonic movements, 2 = moderate myoclonic movements, 3 = major myoclonic movements [16].

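### The Implementation section says participants will be told their randomised allocation, which contradicts the patient blinding stated elsewhere in the protocol

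*Protocol article*

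**What the plan says.** Four parts of the protocol article bear on whether patients know their arm.

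- **Implementation.** "After all the participants have finished the preoperative evaluation and screening", the text continues, "participants will be informed of their randomized allocation". The same section separates the investigator who assesses eligibility and enrols from the one who randomises.
- **Blinding.** "The patients, attending anesthesiologist, and nurse, as well as the researchers, will not be aware of the randomization and allocation concealment throughout the study". Syringes are to be masked with tape.
- **Trial design.** "The trial is a prospective, randomized, controlled, double-blinded, single-center trial". The abstract uses the same label.
- **Allocation concealment mechanism.** A nurse "will open the opaque-sealed envelopes after the participant’s arrival to the operation room".

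Among the secondary outcomes, injection pain is scored "0 = no pain, 1 = verbal complaint of pain, 2 = withdrawal of the arm, 3 = both verbal complaint and withdrawal of the arm". Both primary variables are differences from a baseline reading, T0, which the Interventions section lists ahead of the first reading after induction.

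**The concern.** Staff who follow the Implementation section would tell each patient which drug and dose group they are in. Staff who follow the Blinding section would not. The first course makes the trial open to the patient, whatever its label.

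Three things would be at stake:

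- **Injection pain.** Part of the scale rests on what a conscious patient says. The Background and Discussion both name injection pain as a known drawback of etomidate. A patient who knows the arm could therefore report in an arm-dependent way, most plausibly with more complaints in Group E.
- **Blinding of others.** An informed patient can reveal the arm to the anesthesiologist or the data collector, both of whom the protocol wants blinded.
- **Withdrawal.** The first drop-out criterion is the participant's own request. An informed participant could make that request knowing the arm.

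**Working it through.** This is a textual check. The only arithmetic concerns how many people the sentence covers.

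**1. Number covered.** The Sample size section gives 31 evaluable per group and 20% dropout: 31 / (1 − 0.20) = 38.75, rounded up to 39. Three groups give 3 × 39 = 117, which matches the abstract. If the Implementation sentence were followed for everyone, up to 117 participants would be informed. If the Blinding section were followed instead, none would be.

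**2. Implementation against Blinding.** One says participants are told their allocation; the other names patients first among those kept unaware, for the duration of the study. The disclosure is not qualified anywhere, for example as unblinding after the last measurement. The contradiction is direct and does not depend on exact timing, provided that disclosure comes during the study.

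**3. Implementation against envelope opening.** Disclosure comes after screening; the envelope is opened after arrival in the operating room. The natural reading places disclosure at the end of screening, before the envelope is opened. But "after" screening sets no upper limit, so a patient could be told in the operating room once the envelope is open. The order is therefore unclear, and not necessarily contradictory.

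**4. Which outcomes are exposed.**

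| Outcome | Depends on the patient's awareness? | Exposed when |
|---|---|---|
| Injection pain, grades 1 and 3 | Yes, each needs a verbal complaint | Disclosure at any time before induction |
| Injection pain, grade 2 | Less directly; arm withdrawal only | As above, more weakly |
| T0 for MAP and HR | Possibly; it is listed before induction | Only if disclosure precedes T0 |
| MAP and HR at T1 to T5 | Not directly; taken after induction | Indirectly, if the patient has revealed the arm to staff |

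Injection pain is thus the firm case. T0 is conditional, because the article fixes neither the moment of T0 nor the moment of disclosure.

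**The case against.** The strongest reply is that this is a slip of the pen. Sealed envelopes, taped syringes, a blinded anesthesiologist and a blinded data collector all point to an intention to blind; one sentence points the other way and may have been meant to say that participants are told they will be randomised. That is plausible, and the article does not show that any patient was in fact told. But the sentence refers to the allocation itself, consent is covered separately under Ethics, and Implementation is the section staff would act on. A slip there still needs correcting. Nor is this a detail that an article leaves to a fuller document: the article states two incompatible rules.

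The reply does hold against three stronger readings that a reader might infer:

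- **That allocation concealment is defeated.** Concealment protects the decision to enrol. The disclosure comes after evaluation and screening, and written consent precedes enrolment. Telling a patient already screened breaks blinding, but does not by itself show the recruiter the next assignment.
- **That the primary outcome is biased.** This needs disclosure before T0 and an arm-specific effect of knowledge on MAP or HR. The documents establish neither.
- **That the bias can be put as an inflated false-positive rate.** The article gives no expected pain rate, no size for any shift and no standard deviation for the change in MAP. Any such rate would only restate the assumptions fed into it.

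**Conclusion.** The contradiction is real and is wrong as written: the Implementation section cannot stand beside the Blinding section and the double-blinded label. If it is followed, patient blinding is lost before induction for up to 117 of 117 participants, with injection pain the outcome most exposed and two side routes, disclosure to blinded staff and informed withdrawal. That count is conditional on staff following Implementation over Blinding, which the documents cannot show. The conclusion rests on the ordinary meaning of the two sentences and on the absence of any text placing the disclosure after the study. It claims no size of bias. It should be corrected now, because the Trial status section reports ongoing recruitment and a disclosure cannot be undone.

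**What to change.** Replace the sentence in the Implementation section with wording to this effect: at consent, participants are told only that they will be randomised to one of three regimens; they remain unaware of their allocation until data collection is complete; the envelope is opened in the operating room without disclosure to the patient. This brings Implementation, Blinding and Allocation concealment mechanism into line.

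Then establish whether any participant already enrolled was told their arm:

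- If none was, the correction is enough.
- If some were, report the number, preferably by group, and add a sensitivity analysis of injection pain without them.
- If all were, that analysis has nobody left to analyse, and the trial should be described as not patient-blinded.

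The cost is a one-sentence amendment through the route the protocol already provides (research team and ethics committee), a note to staff, and at most one extra analysis. No additional patients are needed, and no treatment or clinical rule changes.
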